### Criteria for discontinuing or modifying allocated interventions {11b}

Not applicable. Modification and discontinuation of study interventions is described in the previous section.

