## Introduction

### Background and rationale {6a}

Gastric enteral nutrition (EN) is commonly used in critically ill patients who cannot be fed orally [1, 2]. It can be performed with a continuous infusion or the administration of several boluses via a gastric tube. Continuous feeding consists of nutritional infusion at a constant rate. Intermittent nutrition involves administration of a bolus volume delivered over 15–40 min multiple times per day [3]. The rate of continuous infusion or the volume of the bolus is set to meet the daily energetic target. EN begins with the administration of a small amount of nutrition. If the EN is tolerated well, the amount of administered nutrition is increased until the target energy is reached. When signs of intolerance are recognized, the amount of administered nutrition is decreased; thus, the tolerance toward EN determines the time to reach the estimated energetic target—the primary outcome of this study. Both methods have advantages and disadvantages. Continuous administration of nutrients is unphysiologic, does not promote anabolism, and is associated with metabolic complications [4]. However, continuous administration is also associated with fewer gastrointestinal or respiratory complications, and meeting the nutritional targets earlier [5]. Intermittent feeding is physiologic and can promote proteosynthesis. However, it leads to high gastric residual volumes (GRVs) and higher occurrence of diarrhea and aspiration [6]. Studies investigating the effects of the mode of administration on the occurrence of complications and other outcomes have yielded conflicting results [6–9]. The authors of a systematic review of the effectiveness of continuous versus intermittent enteral nutrition have been unable to affirm recommendations for one method over the other [10]. The new guidelines of the European Society for Parenteral and Enteral Nutrition (ESPEN) on clinical nutrition in intensive care units recommend the use of continuous rather than bolus EN. However, the authors assumed that evidence on this issue is very limited, that bolus and continuous feeding are similar in achievement of nutritional targets without either increasing the rate of adverse effects, and that bolus feeding may be a greater stimulus for protein synthesis [11]. On the basis of current knowledge, a clear recommendation for a preferred method of administration of enteral feeding cannot be made [12, 13]. The aim of this study is to determine whether any difference exists in the time to reach the energetic target between two tolerance-driven modes of administration of EN in critically ill adult patients.

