### Intervention description {11a}

The position of the gastric tube will be verified by measurement of gastric pH or abdominal X-ray. Commercial isocaloric formula with a high content of whey-based protein will be used. To eliminate the effects of formula composition on primary and secondary outcomes of the study, the same enteral formula will be used in all patients included in both study arms. Energetic and protein targets will be estimated according to current guidelines, on the basis of body mass index (BMI) and actual body weight (ABW), as summarized in Table 1 [1]. The energy and protein targets will be determined by the study investigator. The study investigator will provide information to the nurse and attending physician regarding the arm of the study to which the patient was assigned, the time of initiation of EN, and the target rate and bolus volume.

Administration of EN begins no earlier than 6 am and no later than 6 pm if signs of intolerance are absent (see below) and the GRV is below 500 mL. Otherwise, the start of EN will be postponed to the time of the next GRV measurement.

EN will be administered in the first arm (CONT) with continuous infusion via an enteral pump with an infusion time of 18 h per day. During the infusion, the patient will be in a 30–40° head-up position. The initial rate of infusion will be set to 25 mL/h and gradually increased every 4 h according to clinical signs of intolerance and GRV measurements. Signs of intolerance will be considered if abdominal distension or pain, vomiting, or diarrhea occur, and if the GRV exceeds 500 mL.

The rate of infusion will be increased according to tolerance and GRV. If there is no sign of intolerance, and the GRV is < 250 mL in two consecutive measurements, the rate will be increased by 25 mL/h until the target rate is reached. If signs of intolerance are absent, and the GRV is 250–500 mL, the current rate will remain unchanged. If intolerance signs are observed, or the GRV is > 500 mL, the rate will be decreased to half until the next assessment of tolerance and GRV.

The daily dose of EN will be divided in the second arm (INT) into six portions administered in 4-h intervals via an enteral pump. The rate of the enteral pump will depend on the volume of the bolus. To avoid sudden gastric distension, the rate will increase with increasing bolus volume [4]. The rates of the enteral pump for particular volumes of EN are summarized in Table 2.

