During the infusion of EN, the patient will be in a 30–40° head-up position. After the administration is finished, the gastric tube will be rinsed with 20 mL of water. The initial volume of the bolus will be 80 mL and will be gradually increased every 4 h according to clinical signs of intolerance and GRV measurements. Signs of intolerance will be considered as abdominal distension or pain, vomiting, diarrhea, and a GRV exceeding 500 mL.

The rate of infusion will be increased according to tolerance and GRV. If there is no sign of intolerance and the GRV is < 250 mL in two consecutive measurements, the volume will be increased by 80 mL/h until the target volume is reached. If intolerance signs are absent and the GRV is 250–500 mL, the current volume of the bolus will remain unchanged. If intolerance signs or a GRV > 500 mL is observed, the volume will be decreased to half until the next assessment of tolerance and GRV.

Measurement of GRV will be performed throughout the entire study period (days 1–5) in 4-h intervals with a 150-mL syringe used for aspiration of gastric content. Volumes lower than 150 mL will be returned to the stomach, and larger amounts will be discarded.

**Table 1 Tab1:** Energy and protein targets

BMI	Energy	BMI	Protein
< 30	25–30 kcal/kg of ABW/24 h	< 30	1.2–2 g/kg ABW/24 h
30–50	11–14 kcal/kg of ABW/24 h	30–40	2 g/kg ABW/24 h
–	–	> 40	2–2.5 g/kg ABW/24 h

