### Relevant concomitant care permitted or prohibited during the trial {11d}

#### Prokinetics of the upper gastrointestinal tract

Prokinetics will be administered if an increase in the rate or bolus volume is not reached in three consecutive assessments of tolerance and GRV measurements, respectively. If the rate or bolus volume is lowered in two consecutive assessments of tolerance and GRV measurements, the administration of prokinetics will also start. The choice and dose of prokinetic agent will be made by the attending physician. The effects of prokinetics will be assessed after 24 h of administration. If intolerance persists and the GRV is below 250 mL, EN will continue on a fixed rate of 25 mL/h in both arms. If intolerance and GRV > 250 mL persist, a postpyloric tube will be inserted, and postpyloric nutrition will commence.

**Table 2 Tab2:** Volumes of boluses and rates of the enteral pump

Bolus volume (mL)	Rate of enteral pump (mL/h)	Time of administration (min)
80	160	30
160	320	30
240	320	45
320	320	60
400	400	60
> 400	400	Until administered

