### Methods in analysis to handle protocol non-adherence and any statistical methods to handle missing data {20c}

No analysis populations are defined for this study. Protocol non-adherence will be assessed by the principal investigator case by case. Patients with major deviations from the study protocol will be excluded from the analysis.

Missing data are not planned to be imputed. However, in the event of substantial missing data for any parameter, a sensitivity analysis using any method of imputation could also be used.

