### Adverse event reporting and harms {22}

The formula of EN used in this study is approved for use in critically ill patients, and no severe adverse events relating to the components of this formula are expected.

Serious adverse events have been reported according to standard rules and standard operating procedures of the coordinating unit. All study participants will be monitored for potential adverse events associated with the administration of EN.

We expect the following adverse events to be associated with the administration of EV.
Tube malposition. Strategies to prevent gastric tube malposition are described in the “Intervention description {11a}” section of the protocol.Gastrointestinal complications (high GRV, diarrhea, or vomiting). Management of high GRV is described in the “Intervention description {11a}” section of the protocol. These complications are considered signs of EV intolerance, which result in a decreased rate/volume of EN administered.Refeeding syndrome. Strategies for prevention and management of refeeding syndrome (RFS) are part of the standard care in participating units. They include daily clinical and laboratory screening for RFS and standard medical management if RFS is diagnosed.

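### The plan states intention-to-treat, but {20c} lets the unblinded principal investigator exclude major deviators from the only planned analysis

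*Protocol article*

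**What the plan says.** On the analysis, Statistical methods {20a} adopts intention to treat for the study data. Section {20c} says that no populations are defined and that "Protocol non-adherence will be assessed by the principal investigator case by case", and it drops those with major deviations. Section {20b} plans no additional analysis, and {17a} says that study and treating staff are not blinded.

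On feeding, {11b} tells the reader that "Modification and discontinuation of study interventions is described in the previous section". The section before it, {11a}, can postpone the start and can raise, hold or halve the feed. On intolerance in the continuous arm, "the rate will be decreased to half until the next assessment of tolerance and GRV"; in the intermittent arm, "the volume will be decreased to half until the next assessment of tolerance and GRV". The two rules that end the assigned mode stand later, in the prokinetics part of {11d}. After starting a prokinetic, "The effects of prokinetics will be assessed after 24 h of administration". Then either a postpyloric tube is placed, or "If intolerance persists and the GRV is below 250 mL, EN will continue on a fixed rate of 25 mL/h in both arms". Section {22} says of high GRV, diarrhea and vomiting: "These complications are considered signs of EV intolerance, which result in a decreased rate/volume of EN administered".

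**The concern.** Intention to treat keeps each randomized patient in the assigned arm whatever happens afterwards. An exclusion for deviating from the protocol uses information that arises after randomization. Here the person who decides knows the arm and may know the feeding course, and the two arms follow different feeding procedures that can fail in different ways. If the arms lose different kinds of patient, the comparison is no longer between the groups as randomized, and a difference in time to target could come partly from who was removed.

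The feeding text adds two smaller uncertainties. A reader sent to {11a} for discontinuation does not find it there. And at the assessment after 24 h of prokinetics, a patient with clinical signs and a low GRV falls under both the {11a} halving and the {11d} fixed rate, with no stated order between them.

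**Working it through.** **1. Which analysis does the exclusion apply to?** {20a} gives one principle, intention to treat. {20c} defines no populations, so there is no separate per-protocol set to carry the exclusion. {20b} plans no additional analysis and {21b} no interim analysis. The only sensitivity analysis mentioned, in {20c}, is optional and concerns imputation of missing data. The exclusion therefore falls on the primary comparison.

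**2. Can the exclusion be informative?** The primary outcome ({12}, {18a}) is the day on which at least 80% of the planned feed is delivered. Any interruption or reduction of feed acts directly on it. As a scale, take feed held at 25 mL/h. Assume 1 kcal/mL for the isocaloric formula, and 18 to 24 h per day because the hours are not stated:
- Delivered: 25 × 18 = 450 to 25 × 24 = 600 kcal/day.
- Lowest 80% threshold at BMI < 30 (Table 1, 25 kcal/kg): 0.8 × 25 × weight. At 60 kg this is 1200 kcal. Even 600 kcal reaches it only at 600 / 20 = 30 kg or less.
- At BMI 30 to 50 (11 kcal/kg): 600 / (0.8 × 11) = 68 kg, so above about 68 kg the threshold is not reached either.

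Patients whose feed is suspended or held this low are thus mostly patients without the event while that lasts. Removing such patients from an arm makes it look faster. Removing patients who were advanced faster than the algorithm allows would do the opposite. The net direction is unknown.

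**3. Does the sample size absorb it?** The total is 300 against 2 × 122 = 244, a margin of 56 (56 / 300 = 18.7%) given for drop-out. It is not an estimate of exclusions. A margin in numbers protects power and does not restore comparability.

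**4. The {11b} reference.** {11a} contains modification rules only. The rules that end the assigned mode (fixed 25 mL/h, postpyloric feeding) are in {11d}. The reference is misdirected.

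**5. The fixed 25 mL/h.** Continuous arm, rate in use r, ratio 25 / r:

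| r (mL/h) | 6.25 | 12.5 | 18.75 | 25 | 50 | 75 |
|---|---|---|---|---|---|---|
| ratio | 4.0 | 2.0 | 1.33 | 1.0 | 0.50 | 0.33 |

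Intermittent arm, bolus in use v, daily volume 6v, against 450 to 600 mL/day:

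| v (mL) | 20 | 40 | 80 | 160 |
|---|---|---|---|---|
| 6v (mL/day) | 120 | 240 | 480 | 960 |
| ratio | 3.75–5.0 | 1.88–2.5 | 0.94–1.25 | 0.47–0.63 |

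Break-even is r = 25 mL/h, and v = 450 / 6 to 600 / 6 = 75 to 100 mL. Measured against the halved dose that {11a} would order for the same sign, 25 mL/h gives more feed when r / 2 < 25, that is r < 50 mL/h. In the intermittent arm this holds when 3v < 450 to 600, that is v < 150 to 200 mL.

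Low rates are reachable. Two consecutive reductions, one of the prokinetic triggers, take 25 to 6.25, 50 to 12.5 and 75 to 18.75 mL/h. Recovery within the 24 h can reverse the result: one step up from 6.25 gives 31.25 mL/h, and 25 / 31.25 = 0.8, a reduction.

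**The case against.** The strongest defence on the analysis is that a journal article condenses the protocol, and that the full document or an analysis plan may define major deviations and a per-protocol set. A missing definition is indeed no finding. But the article goes further: it says that no populations are defined and that deviators are removed. Both conflict with {20a} as written. {20b} is headed as dealing with analyses such as subgroups, so it is weaker evidence than {20c}, yet nothing in it supplies a second analysis. The statisticians' pseudonymized data set ({17a}) does not help, because the principal investigator makes the judgement.

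Three stronger readings are tempting, and the article does not support them.
- A reader might infer that a clinically justified stop will be classed as a major deviation and excluded. No text says so; the decision is left open.
- A reader might infer that the absence of stop criteria is itself a safety defect. A condensed article may leave those to the full protocol and the attending physician. The Discussion also gives a reason for reducing and continuing: interrupting feed for lower GRV leads to underfeeding. That argument concerns GRV thresholds and does not cover every clinical stop.
- A reader might infer that the fixed 25 mL/h is an error, because the Background says "When signs of intolerance are recognized, the amount of administered nutrition is decreased". It can fairly be read as a specific rescue rule that replaces general titration and returns the patient to the continuous arm's starting rate. The large ratios sit on small bases: 6.25 to 25 mL/h is 18.75 mL/h, about 340 mL over 18 h (18.75 × 18 = 337.5). Capping at the rate in use could hold a patient at 6.25 mL/h, about 113 mL/day over 18 h.

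**Conclusion.** The conflict between {20a} and {20c} is wrong as written and should be resolved before analysis. It holds for any major deviation and depends neither on the {11b} reference nor on a stop rule. That the exclusion reaches the primary comparison follows from the article defining no other population. That it can be informative follows from the outcome being delivered feed. How many patients would be excluded, and which arm would gain, cannot be derived from the article, so no bias is asserted, only the opening for one.

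The other two matters are minor clarifications. The {11b} reference points to the wrong section. The fixed rate in {11d} lacks its daily hours and its relation to the {11a} halving; depending on the dose in use it is an increase or a reduction. Whether to cap it at the current rate is a clinical choice for the sponsor.

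**What to change.** In {20c}, state that all randomized patients remain in the primary analysis in their assigned arm, including those whose feeding was suspended, fixed at 25 mL/h or moved to postpyloric feeding. State that any exclusion of major deviators is confined to a sensitivity analysis, with criteria written down and applied without knowledge of outcome. This needs no new measurement, only continued outcome collection for deviating patients, which {18b} already aims at. With no interim analysis planned, it can cover all 300 patients, and any patients already set aside should be restored.

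In {11b}, point to {11d}. In {11d}, give the hours per day for the fixed 25 mL/h and say whether it replaces the {11a} halving at that assessment. These are wording changes through the amendment route in {25}, with a staff briefing. If the sponsor chose to change the rate itself, that could apply only to later feeding (100 of 300 patients were randomized by 1 December 2019) and would leave two regimens within the trial. That cost is a reason to clarify the rule and not to rewrite it.

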### Strategies to improve adherence to interventions {11c}

Administration of EN will be provided by nurses who will receive training before the study begins. During the training, the principal investigator or another responsible member of the study team will present the objectives of the study, the methods of measuring patient height and weight, the protocol of administration of EN in both study arms, the method of measuring GRV, and how other study variables will be assessed and documented in the patient medical records. After the study commencement, re-training will occur every 6 months until the trial ends.

### Relevant concomitant care permitted or prohibited during the trial {11d}

#### Prokinetics of the upper gastrointestinal tract

Prokinetics will be administered if an increase in the rate or bolus volume is not reached in three consecutive assessments of tolerance and GRV measurements, respectively. If the rate or bolus volume is lowered in two consecutive assessments of tolerance and GRV measurements, the administration of prokinetics will also start. The choice and dose of prokinetic agent will be made by the attending physician. The effects of prokinetics will be assessed after 24 h of administration. If intolerance persists and the GRV is below 250 mL, EN will continue on a fixed rate of 25 mL/h in both arms. If intolerance and GRV > 250 mL persist, a postpyloric tube will be inserted, and postpyloric nutrition will commence.

**Table 2 Tab2:** Volumes of boluses and rates of the enteral pump

Bolus volume (mL)	Rate of enteral pump (mL/h)	Time of administration (min)
80	160	30
160	320	30
240	320	45
320	320	60
400	400	60
> 400	400	Until administered

#### Parenteral nutrition

The administration of parenteral nutrition will be associated with institutional standards of care. Parenteral nutrition may be considered if less than 60% of the nutritional goal on days 7–10 is reached.

#### Prokinetics of the lower gastrointestinal tract

The prokinetics of the lower gastrointestinal tract will be indicated by the attending physician any time during the study period in the absence of signs of bowel movements. The choice of agent, dosage, and route of administration will be made by the attending physician.

### Provisions for post-trial care {30}

Not applicable.

The trial period includes the first 5–7 days of critical illness. Administration of EN in this trial will follow current guidelines [1, 11], and participation in the trial carries no additional risks beyond those arising from the critical illness itself.

### Outcomes {12}

The primary outcome of the trial is the time from the beginning of the administration of EN to the time at which at least 80% of the target energy is delivered. This will be reported as the day of EN administration. The Kaplan-Meier time-to-event analysis will be used for the analysis of the primary outcome.

Secondary outcomes:
Time from the beginning of the administration of EN to the time at which at least 80% of the target protein dose is delivered. This will be reported as the day of EN administration. The Kaplan-Meier time-to-event method of analysis will be used for the analysis of this secondary outcome.Achievement of the energetic target. This outcome will be aggregated as the proportion of patients who achieve the energetic target during the study period.Tolerance of EN GRV will be aggregated as the proportion with GRV < 250 mL, 250–500 mL, and > 500 mL. Episodes of vomiting will be aggregated as the proportion of patients with any number of episodes of vomiting. Diarrhea stools will be aggregated as the proportion of patients with diarrhea stool > 1 L/day. The need for postpyloric nutrition will be aggregated as the proportion of patients with this need.Incidence of complications of EN. The number of aspiration episodes will be aggregated as the proportion of patients with any number of episodes of aspiration. VAP will be aggregated as the proportion of patients with confirmed VAP.Total serum protein, albumin, and prealbumin concentrations on days 1 and 5. Serum concentrations of protein, albumin, and prealbumin will be aggregated as the mean.ICU and hospital length of stay. ICU and hospital length of stay will be aggregated as the mean. The day of admission and day of discharge will be counted as 1 day.The 28-day mortality will be evaluated with a Kaplan-Meier curve.

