### Sample size {14}

Studies focused on the primary target of our study are lacking. However, we have identified several studies comparing bolus and continuous administration of enteral feeding. These studies included small numbers of patients, were conducted in different patient populations, and did not assess the time to reach the nutritional targets as a primary outcome. However, for calculation of the sample size, we hypothesized a difference of 1 day between groups (target being reached on day 2 and day 3, respectively). The alpha was set to 5%, and the power was set to 80%. The estimated sample size was 122 patients per arm. To account for potential drop-out, we increased the sample size to 300 participants in total, with 150 patients in each study arm.

**Table 3 Tab3:** Participant timeline

	Study period							Follow-up
Time point	Screening	D0	D1	D2	D3	D4	D5	D28
Number of visits	1	2	3	4	5	6	7	8
Eligibility criteria	x							
Informed consent	x							
Allocation	x							
Demographic data		x						
APACHE II		x						
SOFA score		x						
Laboratory tests (total serum protein, albumin, prealbumin)		x					x	
Estimation of energy and protein target		x						
Administration of enteral nutrition			x	x	x	x	x	
Assessment of tolerance (diarrhea, vomiting, GRV, postpyloric nutrition)			x	x	x	x	x	
Assessment of complications			x	x	x	x	x	
Assessment of energetic and protein targets			x	x	x	x	x	
Assessment of hospital LOS, ICU LOS, and mortality								x

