## Statistical methods

### Statistical methods for primary and secondary outcomes {20a}

For analyses of study data, the intention-to-treat principle will be used.

For analyses of the primary outcome, the Kaplan-Meier curve, log-rank, or Wilcoxon test will be used. Standard descriptive statistics (i.e., number of available values, mean, SD, median, 25% and 75% quartiles, minimum and maximum) will be calculated for continuous variables. Categorical variables will be described by using tables of frequency. Secondary outcome measures will be compared between study groups with the *t* test or Mann-Whitney test as applicable, and the chi-square test will be used for categorical data. Differences in laboratory tests between different days of measurement will be analyzed with paired tests (paired *t* test or non-parametric Wilcoxon test). A Kaplan-Meier curve will be used to demonstrate 28-day mortality. A significance level of 5% will be used for all statistical tests. Confidence intervals will be presented as appropriate.

The data analyses will be performed after completion of the study. Interim analysis is not planned.

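### Kaplan-Meier for time to target, and mean length of stay, are fixed without accounting for death; if deaths or rescued patients are censored, target achievement is overstated and an arm difference can be masked

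*Protocol article*

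**What the plan says.** The section Outcomes {12} defines the primary outcome as the time from start of enteral nutrition (EN) until at least 80% of the energy target is delivered, reported in days. It fixes the method: "The Kaplan-Meier time-to-event analysis will be used for the analysis of the primary outcome". The protein target is handled in the same way. Statistical methods {20a} adds the test: "For analyses of the primary outcome, the Kaplan-Meier curve, log-rank, or Wilcoxon test will be used". Table 3 schedules assessment of the targets on D1 to D5.

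The section on upper gastrointestinal prokinetics describes what follows if intolerance persists 24 h after prokinetics. With a gastric residual volume below 250 mL, "EN will continue on a fixed rate of" 25 mL/h in both arms. With a volume above 250 mL, "a postpyloric tube will be inserted, and postpyloric nutrition will commence".

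For length of stay, Outcomes {12} states: "ICU and hospital length of stay will be aggregated as the mean". Section {20a} allows a t test or Mann-Whitney test for secondary outcomes. Table 3 places "Assessment of hospital LOS, ICU LOS, and mortality" in the D28 column.

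No section names a competing event, gives a censoring rule for the two time-to-target outcomes, or says how deaths enter length of stay.

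**The concern.** Eligibility requires an mNUTRIC score of at least 5 and ventilation expected for at least 72 h, while the target is assessed over five days. Some patients will die, stop EN or leave the ICU before reaching the target. Kaplan-Meier ordinarily censors a patient at such an exit, and so treats that patient as someone who would have gone on to reach the target at the same rate as those still being fed. After death this is impossible, so the curve estimates something higher than the share of patients who reach the target.

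Rescue raises a sharper issue. The Background says that tolerance determines the time to target, and the protocol starts rescue because of intolerance. If patients left the risk set at rescue, the censoring would depend on the outcome. The mode of feeding that causes more rescue would lose its worst patients from the comparison.

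For length of stay, a patient who dies on day 3 contributes a short stay. An arm with more early deaths can therefore look better on the mean.

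**Working it through.** **The plan's own figures.** The protocol gives no death, exit or rescue rates. Its only relevant figures are in Sample size {14}: "we hypothesized a difference of 1 day between groups (target being reached on day 2 and day 3, respectively", leading to 122 per arm. Without an SD or an event distribution, 122 can be neither confirmed nor refuted. Exponential times with medians of 2 and 3 days (hazard ratio 1.5), five days of follow-up, two-sided 5% and 80% power give 127 to 131 per arm, depending on the formula. Nothing below depends on 122. I use only the two times, read as medians.

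**1. Censoring death or exit.** Assume a constant target hazard λ = ln 2 / median and a constant exit hazard c.

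- Kaplan-Meier with exits censored estimates 1 − exp(−5λ).
- The share who actually reach the target by day 5 is λ/(λ+c) × [1 − exp(−5(λ+c))].
- The share who exit first is c/(λ+c) × [1 − exp(−5(λ+c))].

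Worked case: median 2 days, c = 0.05. Then λ = 0.3466 and 1 − exp(−1.733) = 82.3%. The cumulative incidence is 0.3466/0.3966 × [1 − exp(−1.983)] = 75.4%.

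| Median | c per day | Exit first | Kaplan-Meier | Cumulative incidence | Overstatement |
|---|---|---|---|---|---|
| 2 d | 0.02 | 4.6% | 82.3% | 79.4% | 2.9 |
| 2 d | 0.05 | 10.9% | 82.3% | 75.4% | 7.0 |
| 2 d | 0.10 | 20.0% | 82.3% | 69.3% | 13.0 |
| 2 d | 0.15 | 27.7% | 82.3% | 64.0% | 18.4 |
| 3 d | 0.02 | 5.7% | 68.5% | 65.8% | 2.7 |
| 3 d | 0.05 | 13.4% | 68.5% | 62.0% | 6.5 |
| 3 d | 0.10 | 24.4% | 68.5% | 56.5% | 12.0 |
| 3 d | 0.15 | 33.5% | 68.5% | 51.6% | 16.9 |

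The top of the range needs 28% to 34% of patients to exit before reaching the target, which means all exits together and not death alone. For scale only, the increase from 122 to 150 per arm implies a drop-out allowance of 1 − 122/150 = 18.7%, whose causes are not stated.

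**2. Rescue falls inside the window.** Assessments are 4-hourly. Two reductions (8 h) or three assessments without an increase (12 h) start prokinetics, which are reviewed after 24 h. Rescue is thus possible from about 32 to 36 h, on day 2, when the protocol expects targets to be reached. At 25 mL/h a patient receives 450 mL in 18 h or 600 mL in 24 h. Assuming 1 kcal/mL and a 70 kg patient with BMI below 30, 80% of the lowest target in Table 1 is 0.8 × 25 × 70 = 1,400 kcal. Such a patient stays below target.

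**3. What censoring at rescue would do.** Assumptions: 150 per arm; daily chance of reaching target 30% if tolerant and 5% if intolerant; death 3% per day; rescue of intolerant patients at day 2; intolerant share 10% v 30%.

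- Tolerant patients reach the target by day 5 with probability 0.30 × (1 − 0.679^5)/0.321 = 0.800, where 0.679 = 0.70 × 0.97.
- Intolerant patients reach it by day 2 with probability 0.05 + 0.05 × 0.9215 = 0.096, where 0.9215 = 0.95 × 0.97. If followed to day 5, the probability is 0.05 × (1 − 0.9215^5)/0.0785 = 0.214.

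| Handling | 10% intolerant | 30% intolerant | Difference |
|---|---|---|---|
| Censor at death and rescue (Kaplan-Meier) | 81.8% | 78.9% | 2.9 |
| Death and rescue both count as not reached | 0.9 × 0.800 + 0.1 × 0.096 = 72.9% | 0.7 × 0.800 + 0.3 × 0.096 = 58.9% | 14.1 |
| Death not reached; EN followed after rescue | 0.9 × 0.800 + 0.1 × 0.214 = 74.1% | 0.7 × 0.800 + 0.3 × 0.214 = 62.4% | 11.7 |

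Simulated log-rank power (3,000 trials) is 21% under the first handling and 69% under the second. With 10% v 25% intolerant it is 16% v 47%, and with 10% v 20% it is 10% v 24%. A separate simulation under other assumptions (rescue at day 2 in 25% v 10%, arms otherwise equal) gave 20% v 59%. With equal intolerance (10% in each arm), rejection is 4.7% and 5.2%.

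**4. Length of stay.** If a share p of an arm dies early with mean stay d, and the rest stay s on average, the arm mean is p·d + (1 − p)·s. Two arms with the same d and s differ by (p₁ − p₂)(s − d) in favour of the arm with more early deaths. The Mann-Whitney test ranks those deaths as short stays in the same way.

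**The case against.** The strongest reply is that the protocol adopts no harmful censoring rule. A reader might infer that rescued patients are censored and that target achievement is therefore already overstated. The documents do not say so. The analysis is by intention to treat, targets are assessed daily from D1 to D5, and EN volume is taken from the medical records with no stop at rescue. On the natural reading, a rescued patient stays under observation and simply counts as not reached. Postpyloric feeding is still EN, and the endpoint is defined by what is delivered, not by route. If deaths and rescued patients are kept at risk to day 5, one minus Kaplan-Meier equals the cumulative incidence and the bias disappears. All this stands, and it makes the harm conditional.

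It also stands that intolerance is not lost from the trial. The crude proportion achieving the energy target, the need for postpyloric feeding, residual volume categories, vomiting and 28-day mortality are all reported. These are secondary, however, and do not correct the primary curve. Nor is the log-rank test invalid: with non-informative exits it tests the cause-specific hazard, and no type I inflation appears when intolerance is equal.

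A reader might also infer from the D28 column of Table 3 that long stays are cut at day 28. That is inference only, since length of stay is taken from the medical records.

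Finally, a detailed censoring rule may sit in an analysis plan that is not shown. The point is therefore not that a rule is missing. The article fixes methods whose ordinary use censors deaths and averages them in as short stays. Intention to treat settles who is analysed, not how a death before target is coded.

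**Conclusion.** The point holds in conditional form. The named methods do not account for death, in a population where deaths and other exits within five days are plausible. If deaths are censored in the ordinary way, the day-5 proportion reaching target is too high by about 3 to 18 points, for assumed exit hazards of 0.02 to 0.15 per day and constant hazards. If patients were also censored at rescue, power in assumed scenarios would fall from about 60-70% to about 20%; with smaller differences in intolerance, both figures are lower. Every rate is an assumption, because the protocol gives none. Mean length of stay, tested by t test or Mann-Whitney, counts an early death as a short stay whatever the rates.

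The documents do not establish that achievement is overstated as planned, that rescue is censored, or that stays are truncated. This should be fixed before analysis, but it does not undermine the trial.

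**What to change.** - **Both time-to-target outcomes.** Treat death before target as a competing event: not reached, kept in the risk set to day 5. Report cumulative incidence by arm with Gray's test, and give the cause-specific log-rank as a sensitivity analysis.
- **Rescue.** Do not censor at the switch to the fixed rate or to postpyloric feeding. Keep following delivered EN to day 5, with a sensitivity analysis that counts postpyloric feeding as not reached.
- **End of EN or ICU discharge through recovery.** State how these count and add a sensitivity analysis. Classing them as failure is debatable, because it could penalise the arm whose patients recover sooner.
- **Length of stay.** Replace the comparison of means with days alive and out of ICU or hospital to day 28, or with time to discharge alive with death as a competing event.

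The cost is analysis wording. The dates come from records that the investigators already review, and no patient's care changes. The reported proportion reaching target will be lower than a curve with deaths censored would show.
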